### Data analysis

2.8

#### Sample size calculation

2.8.1

The sample size calculation was determined through *a priori* power analysis conducted with PASS (v15.0.5, NCSS, LLC). Using a two-tailed alpha level of 0.05% and 90% statistical power, with equal group allocation (1:1), the computation was derived from the change in the AR symptoms VAS scores after treatment. Preliminary data indicated mean VAS scores of 33.6 (SD = 5.2) and 29.4 (SD = 4.8) for the treatment and control group, respectively. Accounting for a 20% dropouot rate, each group required 33 participants, yielding a total target enrollment of 84 patients.

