#### Primary outcome

2.7.1

Participants will self-report symptom intensity scores before the first treatment and after weekly treatments during the trial. The participants are required to self assess the severity of their four nasal symptoms (sneezing, watery rhinorrhea, nasal congestion, and nasal itching) and 4 non-nasal symptoms (ocular itching, watering, redness, itching of the ears, and/or palate) by using a 10-cm Visual Analogue Scale (VAS) (17) that ranges from “no symptoms” to “worst symptoms ever”. Scores will be assessed at baseline (before treatment initiation) and after each week of treatment.

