#### Analytical methods

2.8.4

Statistical analyses will be conducted utilizing the SAS software package, with statistical significance defined as *P* < 0.05. For continuous data following normal distribution, results will be reported as mean ± SD; non-normally distributed data will be presented as median (IQR). Continuous variables will be assessed by the *t*-test or Mann–Whitney *U*-test. Categorical data will be summarized as frequencies (percentages) and evaluated through *χ*^2^ tests or Fisher's exact tests. Additionally, time-by-treatment interactions will be analyzed employing generalized estimating equations or mixed-effects models. All statistical tests will use a 95% confidence level, considering results significant when *P* values are below 0.05.Rescue medication use will be incorporated as a covariate. To ensure robustness, we will conduct sensitivity analyses. Besides, we wil also do exploratory subgroup analysis stratified by whever they use rescue medication or not.

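### The sample-size paragraph is wrong as written: alpha is printed as 0.05%, 33 per group is labelled as the number after dropout, and the two planning means are not identified as scores or reductions

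*Protocol article*

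**What the plan says.** Section 2.8.1 (Sample size calculation) sets the error rates: "Using a two-tailed alpha level of 0.05% and 90% statistical power, with equal group allocation (1:1"). It says that the calculation rests on how the symptom VAS changed after treatment, and its next sentence gives the inputs: "Preliminary data indicated mean VAS scores of 33.6 (SD = 5.2) and 29.4 (SD = 4.8) for the treatment and control group, respectively". It ends: "Accounting for a 20% dropouot rate, each group required 33 participants, yielding a total target enrollment of 84 patients".

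Three other places bear on this. Section 2.8.4 (Analytical methods) analyses the data "with statistical significance defined as *P* < 0.05" and adds "All statistical tests will use a 95% confidence level". The Methods part of the abstract gives 42 participants in each arm and 84 in all. Section 2.7.1 (Primary outcome) has participants rate four nasal and four non-nasal symptoms "by using a 10-cm Visual Analogue Scale (VAS"), anchored so that a higher mark means worse symptoms. It names no scoring unit and no total score.

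**The concern.** A sample-size paragraph should let a reader recover the number from its inputs. This one does not, for three reasons.

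- **Alpha.** 0.05% is 0.0005, one hundredth of the level at which the trial will be tested. If it were the real design level, the claimed 90% power would be far out of reach with 84 participants.
- **Dropout.** If 33 per group already includes the dropout allowance, the total is 66. If the total is 84, then 33 cannot include it.
- **Planning means.** One sentence speaks of a change and the next of scores, with the acupuncture arm higher. As reductions, the figures favour acupuncture. As post-treatment scores on a scale where higher is worse, they favour sham. Without a unit or a named composite, a reader cannot tie the assumed effect to the outcome that will be analysed.

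**Working it through.** **Inputs (section 2.8.1 unless noted).** Means 33.6 and 29.4; SDs 5.2 and 4.8; two-sided test; power 90%; 1:1 allocation; dropout 20%; alpha 0.0005 as printed, or 0.05 as in section 2.8.4.

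Difference = 33.6 − 29.4 = 4.2.

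Pooled SD = √((5.2² + 4.8²)/2) = √25.04 = 5.004.

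Standardised effect d = 4.2/5.004 = 0.839, so d² = 0.7045.

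**1. Number per group for 90% power.** Normal approximation: n = 2(z₁₋α/₂ + z₁₋β)²/d².

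- alpha 0.05: 2 × (1.960 + 1.282)²/0.7045 = 29.8, so 30 per group. The exact t-test needs 31.
- alpha 0.0005: 2 × (3.481 + 1.282)²/0.7045 = 64.4, so 65 per group. The exact t-test needs 68, or 68/0.8 = 85 randomised per group.

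The article's 33 is close to the 5% result and about half of the 0.05% result. It is matched exactly at 5% if the t-test number is inflated for a Mann–Whitney test, which section 2.8.4 also lists: 31 × π/3 = 32.5, so 33.

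**2. Power at the stated numbers.** Noncentral t with 2n − 2 degrees of freedom and noncentrality d√(n/2), which is 3.41 for n = 33 and 3.85 for n = 42.

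| Evaluable per group | Power, alpha 0.05 | Power, alpha 0.0005 |
|---|---|---|
| 26 | 84.3% | 26.3% |
| 31 | 90.2% | 36.6% |
| 33 | 91.9% | 40.8% |
| 42 | 96.7% | 58.9% |
| 68 | 99.8% | 90.4% |

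The stated 90% power cannot be had at 0.0005 with 33 or 42 per group.

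**3. Dropout arithmetic.**

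- 33 as the number after dropout: 2 × 33 = 66, which is not 84. About 33 × 0.8 = 26.4 per group would remain, with about 84% power at alpha 0.05.
- 33 as the number before dropout: 33/(1 − 0.20) = 41.25, so 42 per group, and 2 × 42 = 84. This matches both the stated total and the abstract.

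**4. Planning means.** The required number depends only on the absolute difference of 4.2, so no sample-size figure reveals whether the means are scores or reductions. Scale does not settle it either:

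- In centimetres, one symptom cannot exceed 10, so 33.6 would need a sum (maximum 40 over four symptoms, 80 over eight).
- In millimetres, a 10-cm line runs from 0 to 100, and both values fit a single rating.

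The article states neither a unit nor a sum.

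**The case against.** The best defence is that these are slips of wording. Section 2.8.4 fixes the 5% level twice, so nobody plans a test at 0.0005, and the low power figures describe a trial that will not be run. The abstract gives 42 per arm, and the inflation from 33 to 42 to 84 is arithmetically sound. This stands: the first two errors do not make the trial too small. It does not rescue the paragraph, which states a wrong alpha and puts the wrong label on 33.

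On the planning means, a reader might infer that the acupuncture arm was assumed to do worse. The article does not support that: the preceding sentence bases the calculation on change, and if the figures are reductions the higher value is the better one. A reader might also infer that values above 10 must be an unstated sum of several VAS ratings. That does not follow, because a 10-cm line may be scored in millimetres. What remains is that quantity, unit and composite are not identified.

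It is also fair to say that the authors' software run may have used a Mann–Whitney adjustment, which would make 33 the 90% figure. The t-test figure of 92% should therefore not be presented as the only possible result.

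**Conclusion.** The concern holds as an error in the stated sample-size justification, not as evidence that the trial is underpowered.

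- **Alpha:** wrong as printed. At 0.0005 the power is about 41% (33 per group) or 59% (42 per group); at 0.05 it is about 92% with 33 evaluable. The slip is almost certainly for 5%.
- **Dropout:** 33 is mislabelled. It is the evaluable number, and 42 per group (84 in total) is the number to randomise.
- **Planning means:** ambiguous rather than shown to be wrong. If they turn out to be post-treatment scores, the assumed effect favours sham and has to be restated.

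The power figures assume a two-sided two-sample t-test on a variable with the stated means and SDs, with every evaluable participant contributing one value. That 84 is adequate rests on alpha being 5%, on the two means being reductions, and on dropout not exceeding 20%.

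**What to change.** Replace the statement with: two-sided alpha 0.05; 33 evaluable participants per group give at least 90% power (about 92% by t-test) for a difference of 4.2 with SDs of 5.2 and 4.8; allowing for 20% dropout, 42 are randomised per group, 84 in total.

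Then check the pilot data and label 33.6 and 29.4 either as post-treatment scores or as reductions from baseline, on a named VAS score with its unit and range. The label should come from the data and not be presumed. If they are post-treatment scores, restate the assumed effect and the power that follows from it.

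The cost is one paragraph and one look at the pilot data. Enrolment does not change if alpha is 5% and the values are reductions.

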#### Randomization

2.8.2

The randomization sequence was generated by an independent statistician using SAS version 9.4 (SAS Institute, Cary, NC, USA) with a block randomization algorithm (block sizes of 4 and 6) to ensure balanced allocation between groups. Participants were stratified by disease severity into two strata (mild vs. moderate-to-severe) according to the ARIA guidelines (2016 revision) (14), Within each stratum, participants were randomized 1:1 to either the treatment or control group. The randomization sequence was concealed in opaque, sequentially numbered envelopes, which were opened only after baseline data collection to ensure allocation concealment (21). To ensure baseline comparability between groups, we monitored the distribution of key variables, including age (18–40 vs. 41–60 years), sex, disease duration (≤5 vs. >5 years), and baseline VAS scores. Any significant imbalances detected during the study were adjusted for in the final analysis using appropriate statistical methods.

#### Blinding

2.8.3

To maintain blinding integrity, all investigators will undergo standardized training and adhere to the institutional segregation protocol. All study personnel—including participants, outcome evaluators, and statisticians—remain unaware of group assignments,except the acupuncturist. After the whole treatment period, blinding efficacy will be assessed by asking participants: “What kind of treatment do you think you received? (a) Real acupuncture, (b) Sham acupuncture, (c) Unsure, (d) Not caring.” The success of blinding will then be evaluated using Bang's blinding index (22).

#### Analytical methods

2.8.4

Statistical analyses will be conducted utilizing the SAS software package, with statistical significance defined as *P* < 0.05. For continuous data following normal distribution, results will be reported as mean ± SD; non-normally distributed data will be presented as median (IQR). Continuous variables will be assessed by the *t*-test or Mann–Whitney *U*-test. Categorical data will be summarized as frequencies (percentages) and evaluated through *χ*^2^ tests or Fisher's exact tests. Additionally, time-by-treatment interactions will be analyzed employing generalized estimating equations or mixed-effects models. All statistical tests will use a 95% confidence level, considering results significant when *P* values are below 0.05.Rescue medication use will be incorporated as a covariate. To ensure robustness, we will conduct sensitivity analyses. Besides, we wil also do exploratory subgroup analysis stratified by whever they use rescue medication or not.

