**Methods:**

This clinical trial features a stratified randomization scheme with 1:1 allocation, single-blind assessment, and a total sample size of 84 participants. After screening for inclusion, qualified subjects with perennial allergic rhinitis will be randomly allocated to treatment group(accepting acupuncture, *n* = 42) or control group (accepting sham acupuncture, *n* = 42). The intervention will last over a 4-week period. The main efficacy outcome is the change in main symptom severity assessed by the Visual Analogue Scale (VAS) after each week of treatment. Secondary outcomes include the Total Nasal Symptom Score (TNSS), Efficacy Index (%) after each treatment session, time to onset of effect, Rhinitis Quality of Life Questionnaire (RQLQ) scores after each week of treatment, and the additional use rate of anti-allergic medications.

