### Rescue medication

2.6

In case participants experience any of the following conditions:VAS score ≥7 for any of the primary nasal symptoms for >2 hours;≥10 sneezing episodes within a 24-hour period;Complete nasal obstruction affecting sleep;Symptoms subjectively evaluated by the patient as severely affecting daily activities or work and becoming intolerable.Supplemental loratadine (Xuesu Shanghai Haini Pharmaceutical Co., LTD, Shanghai, China) will be administered 10 mg every day. All investigators and participants must systematically document: (1) All instances of rescue medication including timing, dosage, and reason for use (2) Adverse reactions to rescue medication including symptom description, severity, duration, assessment of relatedness to the rescue medication, and management measures.

These measures ensure patient safety while maintaining treatment efficacy assessment integrity. Collected data will inform comprehensive therapeutic outcome analyses. Participants will be instructed to refrain from using rescue medication for 24 hours prior to Primary outcomes assessment; If a participant has used rescue medication within 24 hours before a scheduled assessment, the assessment will be postponed until at least 24 hours after the last dose. And rescue medication use will be incorporated as a covariate for both primary and secondary outcomes. This approach adjusts its potential confounding effects on symptom scores. To ensure robustness, we will conduct sensitivity analyses. Besides, we will also do exploratory subgroup analysis stratified by whever they use rescue medication or not. All results will be interpreted with this limitation explicitly stated in the Discussion.

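### No primary VAS analysis fixes baseline VAS and the severity stratum as covariates, and baseline adjustment is left to imbalances found during the study

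*Protocol article*

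**What the plan says.** All references are to the protocol article.

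- **Outcome (Abstract, Methods).** "The main efficacy outcome is the change in main symptom severity assessed by the Visual Analogue Scale (VAS) after each week of treatment". The outcome is a change, so the baseline value is subtracted.
- **Test (2.8.4 Analytical methods).** "Continuous variables will be assessed by the *t*-test or Mann–Whitney *U*-test". The section then adds: "Additionally, time-by-treatment interactions will be analyzed employing generalized estimating equations or mixed-effects models". No baseline variable is named for either.
- **Prespecified covariate (2.6 Rescue medication, repeated in 2.8.4).** "rescue medication use will be incorporated as a covariate for both primary and secondary outcomes".
- **Stratification (2.8.2 Randomization).** "Participants were stratified by disease severity into two strata (mild vs. moderate-to-severe" under the ARIA guidelines. No analysis sentence mentions this stratum again.
- **Baseline adjustment (2.8.2 Randomization).** "we monitored the distribution of key variables, including age (18–40 vs. 41–60 years), sex, disease duration (≤5 vs. >5 years), and baseline VAS scores", followed by "Any significant imbalances detected during the study were adjusted for in the final analysis using appropriate statistical methods". The threshold and the adjustment method are not given.

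**The concern.** Stratifying by severity and collecting baseline VAS pay off in the analysis only if the model uses them. The stated tests do not use the stratum, and they use baseline VAS only by subtraction.

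The rule that would bring baseline VAS into a model looks at the wrong thing. Under proper randomisation, any baseline imbalance is due to chance. Its P value does not show whether the variable predicts the outcome, which is what makes adjustment worthwhile. A strongly prognostic variable that happens to be balanced would be left out, and a weak one that happens to be unbalanced would be put in. The primary model would then differ between realisations of the same trial, by a method chosen after the imbalance is seen.

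The sections also do not fit together. A t-test or Mann-Whitney test cannot include rescue medication use as a covariate, yet 2.6 requires that covariate for the primary outcome. The reader cannot tell which model gives the main result. At stake are precision and a primary analysis fixed in advance.

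**Working it through.** **1. The plan's own sample size.** Inputs from 2.8.1: means 33.6 and 29.4, SDs 5.2 and 4.8, power 90%, dropout 20%.

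- Difference: 33.6 − 29.4 = 4.2.
- Pooled SD: √[(5.2² + 4.8²)/2] = 5.004. Standardised difference: 4.2/5.004 = 0.839.
- Normal approximation, two-sided 0.05: n = 2 × (1.960 + 1.282)² × 5.004²/4.2² = 29.8, so 30 per group. With the t distribution it is 31.
- The stated 33 is reached with a common SD of 5.2 (normal approximation), or with 31 × π/3 = 32.5, the usual Mann-Whitney inflation.
- 33/0.8 = 41.25, so 42 per group and 84 in total, as stated.

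The significance level is printed as 0.05%. Taken literally it would need 65 (normal) or 68 (t) per group, so the calculation used 0.05. That is a separate misprint. None of these variants uses baseline or stratum.

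**2. Precision left unused.** With equal variances at baseline and follow-up and correlation r, the variance of an ANCOVA estimate relative to a change-score t-test is (1 − r²)/[2(1 − r)] = (1 + r)/2. The protocol gives no r, so a range is assumed. The planning SD is read as the SD of the change, because 2.8.1 says the calculation rests on the change in VAS. Power is by the noncentral t at 33 per arm, two-sided 0.05.

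| Analysis | Relative variance | Effective SD | Power |
|---|---|---|---|
| Change-score t-test | 1.00 | 5.004 | 91.9% |
| ANCOVA, r = 0.3 | 0.65 | 4.034 | 98.6% |
| ANCOVA, r = 0.5 | 0.75 | 4.334 | 97.2% |
| ANCOVA, r = 0.7 | 0.85 | 4.613 | 95.4% |

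If the SD is instead that of the final score, the factor is 1 − r². The number per group for 90% power is then 28, 23 or 16 at r = 0.3, 0.5 or 0.7, against 30 unadjusted (normal approximation).

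**3. How often the imbalance rule fires.** Take significant as P<0.05 on each of the four listed variables (age, sex, disease duration, baseline VAS), treated as independent: 1 − 0.95⁴ = 18.5%.

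**4. What the rule recovers.** A simulation used 66 analysed patients, blocks of 4 and 6 within two strata, 40% mild, strata 1.5 SD apart at baseline, and r = 0.5 within stratum. All of these except the block sizes and the 66 (2 × 33) are assumptions. The rule was applied to baseline VAS at P<0.05, with a final-score t-test otherwise. At a standardised difference of 0.839, power was 93.1% for the final-score t-test, 92.5% for the change-score t-test, 93.4% for the imbalance rule, and 98.5% for ANCOVA with baseline and stratum always included. The rule recovers almost nothing.

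**5. Test size when the stratum is left out.** If randomisation balances the stratum and severity explains a share R² of the variance of the analysed outcome, the unadjusted test has an approximate true size of P(|Z| > 1.96/√(1 − R²)). This gives 3.9%, 2.8% and 1.9% for R² = 10%, 20% and 30%; simulations gave 3.9%, 2.6–2.9% and 1.8–2.0%. These figures apply only where severity predicts the outcome analysed. If severity shifts baseline and follow-up equally, it cancels from the change score and the size is about 5%.

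**The case against.** The strongest reply is that the t-test sentence is generic. It covers every continuous variable and is not labelled as the primary analysis. A longitudinal model is named, a covariate is prespecified, and a journal article may leave the model's remaining terms to an analysis plan that is not shown. This stands in part: the absence of a covariate list, or of a choice between GEE and a mixed model, would not be a finding by itself. It does not rescue the imbalance rule, which is stated affirmatively. An analysis plan that fixed baseline VAS in advance would contradict 2.8.2 rather than complete it.

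The word significant may also mean material rather than P<0.05. That is possible, and the 18.5% depends on the P<0.05 reading. Either way the trigger is an observed imbalance, not prognostic value.

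A reader might infer stronger points that the document does not support:

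- *Baseline VAS is ignored.* It is not: the outcome is a change score.
- *Imbalance is the only route to any adjustment.* Rescue medication use is prespecified. It is a post-randomisation variable, so it does not replace baseline adjustment.
- *Unblinded choices decide the result.* Section 2.8.3 keeps statisticians and outcome evaluators unaware of allocation, and a balance check uses no outcome data.
- *The trial is underpowered or its type I error is inflated.* At the plan's own effect the unadjusted test exceeds 90% power, and leaving out the stratum makes the test conservative, if it changes the size at all.

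**Conclusion.** The point holds as a matter of efficiency and prespecification. The stratum is unused, baseline VAS is not a fixed covariate, and the only stated route to baseline adjustment depends on chance imbalance.

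The loss is 35%, 25% or 15% of variance relative to a change-score t-test for r = 0.3, 0.5 or 0.7. On the plan's own effect, this is about 92% power against about 99%, 97% or 95%. These figures assume r, equal variances at baseline and follow-up, and that the planning SD is that of the change. No bias, inflated error rate or missed power target follows, and the planned 84 remains sufficient. The change is well worth making, but the trial does not fail without it.

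**What to change.** - State one primary VAS analysis, either ANCOVA or a mixed model for the weekly scores, with treatment, baseline VAS and severity stratum (mild, moderate-to-severe) as fixed, prespecified terms.
- Delete the imbalance-triggered adjustment in 2.8.2 and report baseline balance descriptively.
- Reword 2.8.4 so that the t-test and Mann-Whitney test are not presented as the comparison for the primary outcome, and so that it agrees with the covariate statement in 2.6.

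Baseline-by-week terms and a preference for a mixed model over GEE are optional. The cost is wording in the protocol and analysis plan, settled before unblinding. All the variables are already collected, and no patient, visit or change in sample size is needed.

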#### Secondary outcome

2.7.2

1.The participants self assess the four nasal symptoms (nasal obstruction, rhinorrhea, sneezing, and itching) involved in assigning the total nasal symptom score (TNSS) (18). The symptoms were graded on a five-point scale (where 0 indicates no symptoms, a score of 1 for mild symptoms that are easily tolerated, 2 for awareness of symptoms which are bothersome but tolerable and 3 is reserved for severe symptoms that are hard to tolerate and interfere with daily activity). Score will be calculated before the treatment and after everytime treatment.2.The efficacy was evaluated according to the improvement of TNSS score

Efficacy index (%) = (TNSS total score before treatment-total score after treatment)/ total score before treatment ×100% (19).

Obvious effect: the nasal symptoms were significantly improved after treatment, and the curative effect was >76%;

Effective: Nasal symptoms improved after treatment, 26%≤curative effect ≤76%;

Ineffective: Nasal symptoms did not significantly reduce after treatment, and the curative effect was <26%.
3.Onset time of effectAfter the treatment begin, the number of treatments will be recorded when the Efficacy index reaches 26%.
4.Quality of life score of AR patients:The participants self assess symtoms by using the Rhinitis Quality of Life Questionnaire (RQLQ) (20), which has 28 questions in 7 items ranked from 0 to 6.

Score will be calculated before the treatment and after weekly treatment.
5.Safety evaluationAdverse events (AEs) will be recorded on the Case Report Form (CRF), including the initial symptom presentation date, recovery timeline, intensity grading, treatment-associated occurrences, and final outcome status (resolution or persistence). AEs associated with acupuncture include needle stagnation, needle fainting, hematoma, or other discomfort. In the event of AEs, the research team will administer necessary medical care and provide corresponding reimbursement, while simultaneously notifying the Data and Safety Monitoring Board for documentation and review.

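### The only test rule for categorical data, chi-square or Fisher, ignores the order of the three efficacy grades and can be significant with neither arm better

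*Protocol article*

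**What the plan says.** Section 2.7.2 of the protocol article defines the Efficacy Index as the percentage fall in TNSS from before to after treatment, and cuts it into three grades:

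- top: "Obvious effect: the nasal symptoms were significantly improved after treatment, and the curative effect was >76" percent
- middle: "Effective: Nasal symptoms improved after treatment, 26%≤curative effect ≤76" percent
- bottom: "Ineffective: Nasal symptoms did not significantly reduce after treatment, and the curative effect was <26" percent

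Section 2.8.4 gives one rule for categories: "Categorical data will be summarized as frequencies (percentages) and evaluated through" chi-square or Fisher's exact tests. It names no trend, rank or ordinal method for them. The Mann-Whitney test appears only in the sentence beginning "Continuous variables will be assessed by the", as the alternative to the t-test. The same section names generalized estimating equations or mixed-effects models for time-by-treatment interactions, without tying them to an outcome.

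The abstract lists the index itself, as a percentage, among the secondary outcomes: "Secondary outcomes include the Total Nasal Symptom Score (TNSS), Efficacy Index (%) after each treatment session". The document gives no expected rates for the three grades and no power for this outcome.

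**The concern.** The grades are cut points on one scale, so they have an order, and the trial asks whether acupuncture does better than sham. A Pearson chi-square test on 2 degrees of freedom, or Fisher's exact test on the 2x3 table, asks only whether the two distributions differ in any way. The result would be the same if the three labels were permuted. Two things follow:

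- **Interpretation.** A small p-value may reflect one arm having more patients at both extremes, which is not evidence of benefit. The test also yields no single effect estimate with a confidence interval.
- **Power.** One of the two degrees of freedom goes to patterns without direction. If treatment moves patients up the whole scale, a test that uses the order detects this more often.

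**Working it through.** **Inputs from the protocol article.** Three ordered grades (section 2.7.2); the chi-square or Fisher rule and significance at 0.05 (section 2.8.4); 42 randomised per arm (abstract); 33 per group and 20% dropout (section 2.8.1). Everything about grade rates below is assumed.

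**The plan's own figure.** The only sample size is for the primary VAS outcome.

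- Pooled SD = √((5.2² + 4.8²)/2) = √25.04 = 5.004.
- Standardised difference = (33.6 − 29.4)/5.004 = 0.839.
- With two-sided alpha 0.05 and 90% power this needs 30 per group (normal approximation) or 31 (t-test). A Mann-Whitney efficiency adjustment gives 31 × π/3 = 32.5, so 33.
- 33/0.8 = 41.25, so 42 per group and 84 in total.

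The stated size is thus reproduced if 33 is the number before dropout and alpha is 0.05. It says nothing about the grades. It only sets the range of 33 to 42 per arm used below.

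**Step 1: significant without direction.** Take 42 per arm, in the order ineffective/effective/obvious: arm A 13/24/5, arm B 20/9/13.

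- Column totals are 33/33/18, so the expected counts per arm are 16.5/16.5/9.
- Chi-square = 2 × (3.5²/16.5 + 7.5²/16.5 + 4²/9) = 2 × (0.742 + 3.409 + 1.778) = 11.86. On 2 df, p = exp(−11.86/2) = 0.003.
- Mean grade, scored 0, 1, 2: A = (24 + 10)/42 = 0.81; B = (9 + 26)/42 = 0.83.
- Rank-sum, counting ties as one half: U for A = 13×20/2 + 24×20 + 24×9/2 + 5×29 + 5×13/2 = 130 + 480 + 108 + 145 + 32.5 = 895.5, against 882 under no difference (42×42/2).
- Tie-corrected variance = (1764/12) × (85 − 77622/6972) = 10858, so z = 13.5/104.2 = 0.13 and p = 0.90.

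The planned type of test declares a clear difference although neither arm is better. This step shows that it can happen, not how often.

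**Step 2: power when all grades shift together.** Simulation at two-sided 0.05, Pearson chi-square against the tie-corrected rank-sum test. First model: a shift on a latent normal scale, with assumed sham splits from 30/50/20 to 60/30/10.

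| Per arm | Shift | Chi-square | Rank-sum |
|---|---|---|---|
| 42 | 0.6 SD | 56–58% | 66–69% |
| 42 | 0.84 SD | 86–87% | 92–93% |
| 33 | 0.6 SD | 45–47% | 55–58% |
| 33 | 0.84 SD | 76–78% | 84–86% |

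Second model: a common odds ratio (OR) at both cut points, 40,000 tables per setting, 33 and 42 per arm, six assumed sham splits (among them 50/40/10, 70/25/5 and 33/34/33).

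| Odds ratio | Rank-sum gain (points) |
|---|---|
| 2 | 6.4 to 8.6 |
| 2.5 | 9.2 to 11.1 |
| 3 | 9.6 to 11.0 |
| 4 | 5.8 to 9.0 |
| 5 | 2.8 to 5.9 |

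One case in full: sham 50/40/10 and OR 3. The odds of ineffective fall from 1 to 1/3, giving 25%. The odds of obvious effect rise from 0.1/0.9 to 0.333, giving 25%. So the treatment arm is 25/50/25. With 42 per arm, chi-square has 64.9% power and rank-sum 74.7%, a gain of 9.8 points.

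**Step 3: power when only the lower boundary moves.** Sham 50/40/10, no change in obvious effect.

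| Treatment split | Per arm | Chi-square | Rank-sum | Chi-square lead (points) |
|---|---|---|---|---|
| 30/60/10 | 33 | 33.5% | 29.0% | about 4.6 |
| 30/60/10 | 42 | 39.8% | 35.2% | 4.6 |
| 20/70/10 | 33 | 68.1% | 57.9% | 10.2 |
| 20/70/10 | 42 | 78.3% | 67.7% | about 10.7 |

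Here the ranking of the two tests reverses.

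**The case against.** **The article never says that the three grades will be compared by a 2x3 chi-square test.** That is correct. The reading joins a general rule to a definition in another section. Three other readings are open:

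- The index can be analysed as a percentage by t-test or Mann-Whitney, which keeps more information than the grades.
- The grades can be collapsed at 26% into a responder rate. That cut also defines onset of effect, and the Discussion cites a single effective rate of 52.1%. Chi-square on a 2x2 table is standard and directional.
- Section 2.6 promises rescue medication as a covariate for secondary outcomes. A plain chi-square test cannot carry a covariate, so it may not be the whole analysis.

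What remains is that the article defines three grades, does not say they will be collapsed, and names no other between-arm test for categories.

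**This is detail for the analysis plan.** That would be so if the article were silent. It states a rule, and the rule does not suit graded data.

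**A reader might infer that the chi-square test simply costs 6 to 11 points of power.** The documents do not support that. They give no grade rates for either arm. The gain needs a shift across the whole scale, falls to about 3 to 6 points at OR 5, and reverses in step 3.

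**A reader might also take 0.84 SD as the protocol's assumed effect here.** It comes from the primary VAS figures and is not an assumption about TNSS grades.

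**The example in step 1 is constructed.** It needs one arm to gain at both extremes, and the reported percentages would show that pattern. That is fair, and it limits the harm without making the p-value answer the trial's question.

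**Conclusion.** The point holds in a limited form. If the stated rule is applied to the three grades, the test ignores their order, gives no single directional effect, and can be significant with neither arm better. That part needs no assumption about rates.

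The power statement is conditional. With 33 to 42 per arm and a moderate common shift (0.6 to 0.84 SD, or OR about 2 to 4, under the assumed sham splits), a rank test gains about 5 to 11 points. The gain shrinks for larger effects. If patients move only from ineffective to effective, the rank test loses about 4 to 11 points. The case for changing the test therefore rests first on interpretation and only second on power.

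Priority is low. This is a grouped form of one secondary outcome, the continuous Efficacy Index can also be analysed, and the primary VAS analysis is not affected.

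**What to change.** Add one sentence to section 2.8.4 stating that the three ordered efficacy grades will be compared between arms in one of two ways:

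- by the Wilcoxon/Mann-Whitney test with tie correction, which the section already names for continuous data; or
- by proportional-odds regression with treatment and the severity stratum used in randomisation, reporting a common odds ratio with its 95% confidence interval.

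Keep chi-square or Fisher's exact test for unordered or two-level data, and go on reporting the three percentages per arm.

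The cost is the sentence; no new data are needed. There are two downsides: some power is lost if only one grade boundary moves, and the odds-ratio version assumes proportional odds, which the rank test does not.
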